### Recruitment

We will recruit for the study through various channels in order to maximise the chances of reaching as many people with dementia as possible. We will recruit through NHS Memory Assessment Services by publicising the study to people who have recently been diagnosed with dementia. We also have agreement from the Alzheimer’s Society to advertise the study to people who are currently on the waiting list in the area for Singing for the Brain sessions. We will harness the support of local community organisations, charities and the local press, and will also use targeted social media advertising. Recruitment will also be undertaken using the online platform “Join Dementia Research”.

### Data collection

#### Quantitative data

Outcome measures will be administered to participants during home visits arranged at times convenient to them. Each visit is expected to take up to 2 h. Baseline data collection will be conducted by BD, and follow-up data collection by blinded researchers. All researchers undertaking data collection will have been fully trained in the administration of these instruments.

The following outcome measures have been selected for use in the study. These are summarised in Table 1, which also shows whether each measure corresponds to the person with dementia, the carer, or both, as well as who completes the measure (the person with dementia, or the carer, either self- or proxy-rating). All outcome measures will be administered at each of the three-time points. Additionally, demographic data will be collected from people with dementia (age, sex, diagnosis, date of diagnosis, ethnicity, education, musical/singing experience) and from carers (age, sex, ethnicity, education, musical/singing experience) at baseline. Measures will be completed by the person with dementia themselves and/or via a proxy rating by the carer. The carer will complete outcome measures about their own mood, quality of life and experience of caring. Some of these measures will be administered by interview and some will be self-completed by the carer.

**Table 1 Tab1:** Summary of outcome measures

Instrument name	Domain measured	Participant		Respondent		
		Person with dementia	Carer	Person with dementia	Carer (proxy)	Carer (self)
QoL-AD	Quality of life	x		x	x	
EQ-5D-5L	Health-related quality of life	x	x	x		x
DEMQOL	Quality of life	x		x		
BADLS	Activities of daily living	x			x	
CSDD	Depression	x		x	x	
GDS	Depression	x	x	x		x
MuseEQ	Musical engagement	x		x		
ADAS-Cog	Cognition	x		x		
CDR	Dementia severity	x		x	x	
QCPR	Caring relationship		x			x
COPE	Experiences/consequences of caring		x			x
SSCQ	Experiences of caring		x			x
CSRI	Use of health/social care	x	x		x	x

A large number of outcome measures are included in this study, in order to assess which of them might be most suitable for future use in a full trial. We recognise that data collection may be time-consuming and tiring for participants, and consequently missing data and incomplete measures are expected in some cases. The order and format of the administration of outcome measures is given in Table 2. This order has been chosen so that instruments measuring similar domains are separated, to maximise the range of information included in incomplete data sets. The interview with the carer will take place first, and subsequently the person with dementia will be interviewed whilst the carer does the self-completed outcome measures.

**Table 2 Tab2:** Order and format of outcome measure administration

Person with dementia (by interview)	Carer	
	By interview	Self-complete
1. QoL-AD 2. GDS 3. CDR 4. MuseEQ 5. ADAS-Cog 6. EQ-5D-5L 7. CSDD 8. DEMQOL	1. QoL-AD proxy 2. GDS 3. CDR 4. QCPR 5. CSRI	1. COPE 2. SSQC 3. EQ-5D-5L 4. BADLS

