### Endpoints

Since PRESIDE is a feasibility study, the endpoint is the attainment of the feasibility criteria at 6 months. The proposed criteria for proceeding to a full trial are 70% recruitment; 70% retention of participants over 3 months; and acceptability of the control condition demonstrated by 70% of the waiting-list participants starting singing groups after being on the waiting list. The acceptability of the control condition is considered to be the most important of these three criteria since this ensures the heterogeneity of the sample. The other feasibility criteria are considered negotiable.

An additional endpoint for PRESIDE is the measurement of quality of life, activities of daily living, mood, musical engagement and cognition of people with dementia, and the measurement of quality of life, mood, caring relationship and experience of caring for the carers of the people with dementia. Each dyad’s use of health social care services and resources will also be documented. Additionally, qualitative data will be collected using interviews and participant observation, in order to better understand the experiences of dyads who attend the singing groups.

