##### Bristol activities of daily living scale

The 20-item scale presents the respondent with various descriptions of performance at activities such as cooking, hobbies and personal care, and asks them to rate the person with dementia’s current level of performance [25]. It will be completed as a proxy rating by the carer. Each items is scored on a scale of 0 to 3, and gives a total score out of 60, where a higher score means a higher level of impairment.

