##### Carers of older people in Europe scale

The 15-item scale asks the carer about their experiences of caregiving and its consequences for their physical and mental health [33]. The responses are scored from 1 (never) to 4 (always). The 15 questions are presented together, but when total scores are calculated they are divided into three subscales which are treated separately in analysis: negative impact of caregiving, positive value of caregiving and quality of support. The precedent for the use of these subscales in analysis is set in one of the paper describing the original development of COPE [34].

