##### Short sense of competence questionnaire

The SSCQ is derived from the Zarit Burden Inventory and evaluates the carer’s experience of caring across seven items [35]. The carer indicates how strongly they agree with the statements in the scale and each item is scored from 1 to 5. A higher score indicates a higher perceived sense of competence.

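### The carer self-completion order in Table 2 breaks the protocol's own separation rule: COPE and SSCQ, both on the experience of caring, come first and second, and the only activities-of-daily-living form comes last

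*Protocol article*

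**What the plan says.** Under Quantitative data, the protocol article accepts that long visits will leave some measures incomplete. It says the administration order was set so that "instruments measuring similar domains are separated, to maximise the range of information included in incomplete data sets". The carer is interviewed first. The carer then fills in four forms alone while the person with dementia is interviewed. Table 2 numbers those forms "1. COPE 2. SSQC 3. EQ-5D-5L 4. BADLS".

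Table 1 gives the domain of COPE as "Experiences/consequences of caring" and that of SSCQ as "Experiences of caring". The instrument descriptions agree: COPE "asks the carer about their experiences of caregiving and its consequences for their physical and mental health", and SSCQ "evaluates the carer’s experience of caring across seven items".

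BADLS is the only instrument that Table 1 assigns to activities of daily living. Of its source the protocol says: "It will be completed as a proxy rating by the carer". The Endpoints section lists, as an additional endpoint, the "measurement of quality of life, activities of daily living, mood, musical engagement and cognition of people with dementia". The carer's EQ-5D-5L appears only in this self-complete column, and the EQ-5D-5L section says the instrument will supply QALYs for both members of the dyad.

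**The concern.** The rule and the table that is meant to apply it disagree. If incomplete sets are to span many domains, two forms on the same domain should not stand together at the head of the list. Here they do, and two domains that no other carer form covers, the carer's health-related quality of life and the daily functioning of the person with dementia, come after them.

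At stake is secondary outcome data. BADLS is lost whenever a carer stops early, and nothing else in the battery supplies that score. The carer EQ-5D-5L is also lost if the carer stops after the first or second form. The study is meant to show which measures suit a full trial, so a form that looks poorly completed because of its place in the list could be misjudged.

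**Working it through.** **1. Is the rule kept in each column of Table 2?** Each instrument is matched to its Table 1 domain.

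- Person with dementia (interview): the quality-of-life measures QoL-AD, EQ-5D-5L and DEMQOL stand at 1, 6 and 8, and the depression measures GDS and CSDD at 2 and 7. No neighbours share a domain, so the rule is kept.
- Carer (interview): QoL-AD proxy, GDS, CDR, QCPR, CSRI. No neighbours share a domain, so the rule is kept.
- Carer (self-complete): COPE and SSCQ stand at 1 and 2 and share the domain of caring experience. The rule is broken.

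**2. Domains covered if the carer stops after k forms.** The three domains are caring experience (COPE, SSCQ), health-related quality of life (EQ-5D-5L) and activities of daily living (BADLS).

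| Order | k=1 | k=2 | k=3 | k=4 | Sum |
|---|---|---|---|---|---|
| COPE, SSCQ, EQ-5D-5L, BADLS (Table 2) | 1 | 1 | 2 | 3 | 7 |
| COPE, EQ-5D-5L, BADLS, SSCQ | 1 | 2 | 3 | 3 | 9 |

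Over all 24 orders of the four forms the sum runs from 7 to 9. Table 2 is at the minimum, shared only with the other orders that put COPE and SSCQ in the first two places (2 × 2 = 4 orders). Twelve orders separate the pair. Eight of those reach 1, 2, 3, 3; the other four leave EQ-5D-5L or BADLS last and give 1, 2, 2, 3.

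**3. What is lost on stopping, in the Table 2 order.** After form 1 or 2: carer EQ-5D-5L and BADLS. After form 3: BADLS only.

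**4. Size, under assumed stopping rates.** The protocol gives no rate, so there is no stated figure to reproduce. Two simple models bracket the effect.

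*Equal per form.* Let s be the chance of stopping after each form. Covering all three domains needs four forms in the Table 2 order, (1−s)³, and three in the alternative, (1−s)². At s = 0.10: 0.9³ = 0.729 against 0.9² = 0.810.

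*By item count.* Lengths from the instrument descriptions are COPE 15, SSCQ 7, EQ-5D-5L 6 (five questions plus the visual analogue scale) and BADLS 20, total 48. Let F be the full-completion probability. A form that ends at item m is completed with probability F^(m/48). All three domains are covered at item 48 in Table 2, and at item 15 + 6 + 20 = 41 in the alternative. With F = 0.729: 0.729^(41/48) = 0.763.

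| Assumed full completion, F | Three domains, Table 2 | Alternative, by items | Alternative, equal per form |
|---|---|---|---|
| 0.857 (s = 0.05) | 86% | 88% | 90% |
| 0.729 (s = 0.10) | 73% | 76% | 81% |
| 0.512 (s = 0.20) | 51% | 56% | 64% |

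**5. By form, item model, F = 0.729.**

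- Carer EQ-5D-5L ends at item 28 now and at 21 in the alternative: 0.729^(28/48) = 0.83 against 0.729^(21/48) = 0.87.
- BADLS ends at 48 now and at 41 in the alternative: 0.73 against 0.76.
- SSCQ ends at 22 now and at 48 in the alternative: 0.729^(22/48) = 0.87 against 0.73.

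**The case against.** The strongest reply is that the effect is small and its size unknown. No stopping rate is given. The larger gain, 73% to 81%, depends on a 7-item form costing the carer as much as a 20-item one. When length is counted, the gain is about 3 points. Carers working alone may also not follow the printed order. All of this stands, and it is why the percentages can only be illustrations. It does not remove the mismatch, because the protocol numbers the forms and justifies the numbering.

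It can also be said that COPE and SSCQ are not duplicates. COPE yields three subscales that are analysed separately, and SSCQ scores perceived competence. The overlap is therefore partial, but the rule concerns similar domains, and Table 1 labels the two almost alike.

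The choice of remedy matters too. Putting BADLS second and EQ-5D-5L third would leave EQ-5D-5L third and move its end from item 28 to item 15 + 20 + 6 = 41. That criticism is sound against that order. It does not apply to COPE, EQ-5D-5L, BADLS, SSCQ.

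A reader might infer more than the text supports, in three ways:

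- That a short interview with the person with dementia cuts the carer's time. The protocol says only that the two run in parallel. Six of the eight interview instruments alone total 13 + 15 + 35 + 6 + 19 + 29 = 117 items, against 48 for the carer, and nothing says the carer must stop when the interview ends.
- That every early stop loses both late forms. After the third form only BADLS is lost.
- That health-related quality of life disappears from the dyad. The person with dementia gives their own EQ-5D-5L by interview, and carer mood, relationship quality and service use are collected earlier, also by interview.

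**Conclusion.** The concern holds as a minor internal contradiction. The stated rule is kept in two columns of Table 2 and broken in the third, which suggests an oversight. The carer self-complete order gives the lowest domain coverage that any order of these forms can give, and it places the sole source of a named endpoint where any early stop loses it.

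That conclusion rests on Table 1's own domain labels and on forms being completed in the numbered order; it needs no stopping rate. The size does need one. For assumed full completion between 51% and 86%, the gain in covering all three domains is about 2 to 5 points if stopping follows item counts, and about 5 to 13 points if it is equal per form.

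The three primary feasibility criteria (recruitment, retention and acceptability of the waiting list) do not depend on the order of these forms, so the point does not bear on the decision to proceed to a full trial through those criteria.

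**What to change.** Reorder the carer self-complete column to COPE, EQ-5D-5L, BADLS, SSCQ, and use that order at all three time points. This separates the two caring-experience forms and moves both EQ-5D-5L and BADLS earlier. Correct SSQC to SSCQ in the same edit.

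The number of forms and items does not change, so there is no added burden. The price is that SSCQ becomes the form most likely to be missed; COPE still covers that domain, which is the trade the stated rule intends. On the article's account, recruitment was paused in March 2020, before the first group planned for late April, and baseline data are not collected until groups are about to start. On that account the change would disturb no data already collected. If the present order is deliberate, the sentence stating the rule should instead be limited to the columns where it applies, with the reason given.

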##### Quality of life—Alzheimer’s disease scale

This 13-item measure asks respondents to rate various aspects of the person with dementia’s life as poor, fair, good or excellent [20]. It will be completed by participants with dementia, and a proxy rating will also be provided by the carer. Each item is scored on a scale from 1 to 4, so the measure yields a total score out of 52, where a higher score indicates a higher quality of life.

##### EQ-5D-5L

This instrument comprises five questions about health-related quality of life, and a visual analogue scale [21–23]. It will be completed by participants with dementia and carers. The results will be used to calculate Quality-Adjusted Life Years (QALYs) for all participants. The first five questions are scored on a five-point scale and generate a five-digit health state for each participant (e.g. a score of 12345 would indicate no problems with mobility, slight problems with self-care, moderate problems doing usual activities, severe pain or discomfort, and extreme anxiety or depression). The visual analogue scale is the final item of the EQ-5D-5L and asks respondents to rate their current health as a point on a line. This gives a score out of 100, where a higher score indicates a higher perceived level of overall health.

##### Dementia quality of life

This scale asks the person with dementia to rate their quality of life by responding to 29 questions about their feelings, memory and everyday life [24]. The respondent selects ‘a lot’, ‘quite a bit’, ‘a little’ or ‘not at alL’ in response to each question. Each question is scored on a scale from 1 to 4, giving a total score out of 116 where a higher score indicates a higher quality of life.

##### Bristol activities of daily living scale

The 20-item scale presents the respondent with various descriptions of performance at activities such as cooking, hobbies and personal care, and asks them to rate the person with dementia’s current level of performance [25]. It will be completed as a proxy rating by the carer. Each items is scored on a scale of 0 to 3, and gives a total score out of 60, where a higher score means a higher level of impairment.

##### Cornell scale for depression in dementia

The 19-item scale assesses symptoms of depression in people with dementia and their severity [26]. It is completed through interviews conducted with the person with dementia and the carer separately, with the interviewer assigning a score based on the severity of symptoms within the past week. For each indicator of depression, absent symptoms score 0, mild or intermittent symptoms score 1, and severe symptoms score 2. The total score is out of 38, where scores above 10 indicate probable major depression, and scores above 18 indicate definite major depression.

##### Geriatric depression scale

The 15-item version of this scale presents the respondent with ‘yes/no’ questions about how they have been feeling over the past two weeks [27]. It will be completed by people with dementia and carers. Each answer indicative of depression scores one point. A score of 5 or higher is suggestive of a depressive disorder, whilst a score of 10 or higher is indicative of a probable depressive disorder.

##### Musical engagement questionnaire

This scale has 35 items that ask the participant how they have used and engaged with music over the past month [28]. It will be completed by people with dementia. The scale consists of statements such as ‘I play a song over and over if I like it’ and the respondent indicates the extent to which they agree with the statement on a five-point scale, scored from 1 to 5. The total score is out of 175, and a higher score indicates a higher level of musical engagement.

##### ADAS-Cog

The measure assesses a number of facets of cognitive performance including memory, verbal skills, motor skills, and orientation [29, 30]. It will be completed by the person with dementia. The tests include memorising a list of words, naming familiar objects as they are presented, copying drawn shapes and following verbal instructions. The interviewer also rates the participant on their verbal fluency, comprehension and ability to concentrate. The total possible score is 70, with higher scores indicating higher levels of cognitive impairment.

##### Clinical dementia rating

This instrument gathers data through semi-structured interviews conducted with the carer and the person with dementia [31]. The interviewer uses this data to rate the severity and stage of dementia across six different domains: memory, orientation, judgement/problem solving, community affairs and home/hobbies. The rating of each of these domains is used to generate an overall CDR score which indicates the level of impairment present: 0 (none), 0.5 (questionable), 1 (mild), 2 (moderate) or 3 (severe).

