### Allocation and blinding

Participants will be recruited in pairs consisting of a person with dementia and a carer. They will be randomised in pairs to either the intervention group or the waiting-list control group. Randomisation will be stratified by sex and Clinical Dementia Rating (CDR). Randomisation will be carried out using a web application created by the trial programmer at the University of Nottingham Stroke Trials Unit, using web and database servers provided by University of Nottingham Information Services (IS). The researcher (BD) will use this web application to randomise each participant. The system will hide information relating to the intervention groups from other users until explicitly granted access by the trial programmer, for example, when a statistician requires unblinded data.

Dyads will be randomly allocated to intervention or waiting-list control groups by the web-based system. BD will collect baseline data prior to randomisation, and so will be unaware of allocation until the initial data collection is complete. Thereafter, both the researcher (BD) and the participants will be aware of the group allocation, along with those delivering the sessions. Due to the nature of the intervention and control groups, it is not feasible to blind participants to group allocation; they will know whether they are attending singing group sessions. The research team will be split into two groups, which will define their access to data and to group allocation. The data management group will be responsible for the data collection and running of the study, and will not be blinded to group allocation once baseline data collection has taken place. The data analysis group will be responsible for conducting the analysis, and will remain blinded to group allocation for the duration of the study. The data analysis group will not have any contact with study participants.

Follow-up data collection will be undertaken by researchers who are blinded to group allocation. However, since the participants will know their own group allocation, there is a possibility that they will reveal this during the follow-up data collection. Unblinding of outcome assessors which occurs in this way will be recorded. All researchers undertaking data collection will have been fully trained in the administration of these instruments.

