### Data coding and analysis

#### Statistical analysis of quantitative data

Quantitative data analysis will be conducted by the study statistician (BG), using the software package Stata 16. The data analysis will be mainly descriptive [38]. All measures will be summarised with mean and standard deviation (S.D.) for normally distributed variables, median and inter-quartile range (IQR) for skewed variables, and frequency (%) for response of categorical variables, by intervention arm across follow-up time. Analysis of Co-variance (ANCOVA) will be performed to quantify treatment effect size and its precision by means of regression modelling with baseline measures as covariate, and to derive the change from baseline score for each arm. Due to the non-independence of patient-carer dyad measures and with data being measured repeatedly, multivariate, multilevel modelling will be performed to account for the association between the same kind of outcome measure of patient-carer data and repeated data. We will calculate recruitment rate, retention rate and attrition rate, exploring patterns of missing data and drop out from the intervention group and the waiting list control group. All results will be used to inform future definitive trial design.

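### CDR is a repeated outcome but is scored only as an overall five-level stage, which is a coarse basis for judging whether it suits the full trial

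*Protocol article*

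**What the plan says.** Table 1 of the protocol article (Data collection, Quantitative data) lists CDR as an outcome measure for the person with dementia, under the domain "Dementia severity". The text above the table says: "All outcome measures will be administered at each of the three-time points".

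The Clinical dementia rating section describes separate semi-structured interviews with the carer and the person with dementia, from which the interviewer rates six domains. It then says: "The rating of each of these domains is used to generate an overall CDR score". The result is an "overall CDR score which indicates the level of impairment present: 0 (none), 0.5 (questionable), 1 (mild), 2 (moderate) or 3 (severe". No other CDR summary is described.

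CDR has a second role under Allocation and blinding: "Randomisation will be stratified by sex and Clinical Dementia Rating (CDR".

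The statistical analysis section is mainly descriptive. It also says, without naming instruments: "Analysis of Co-variance (ANCOVA) will be performed to quantify treatment effect size and its precision by means of regression modelling with baseline measures as covariate". The Quantitative data section explains that many measures are included "in order to assess which of them might be most suitable for future use in a full trial".

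**The concern.** An overall stage works well as a stratification factor, where a few broad groups are wanted. As an outcome followed over 3 and 6 months it is blunt. By the article's own labels, mild and moderate correspond to stages 1 and 2, so the sample is likely to be concentrated on two values at baseline. A participant counts as changed only after moving a full stage. Smaller shifts in one or two domains would be rated by the interviewer but could leave the overall stage where it was.

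What is at stake is the screening of measures for the full trial. If CDR shows almost no movement, the team could not tell whether the instrument is unresponsive in this population or whether its scoring hid the movement. CDR also takes interview time. Table 2 places it third in both the person's and the carer's interview, ahead of MuseEQ, ADAS-Cog, EQ-5D-5L, CSDD and DEMQOL for the person with dementia, in a visit of up to 2 hours that the article expects to be tiring.

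**Working it through.** The article gives no effect size, standard deviation, rate of stage change or power for CDR, so there is no stated figure to reproduce. The check has two parts: a count of levels from the text, and an illustration under assumed rates.

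**Levels**
- Overall score: 0, 0.5, 1, 2, 3, which is five levels.
- Levels whose labels match the entry criterion (mild or moderate): 1 and 2.
- Levels one step away at follow-up: 0.5 or 2 from stage 1, and 1 or 3 from stage 2. At least four levels (0.5, 1, 2, 3) can therefore occur after baseline.
- The overall stage is generated from the domain ratings, so it cannot change unless at least one domain rating changes. The reverse does not hold, because five levels cannot distinguish all patterns of six ratings.
- If each domain is rated from 0 to 3 (assumed; the article does not give the domain scale), the sum runs from 0 to 6 × 3 = 18.

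**Illustration**

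Inputs: 40 dyads per arm (Sample size section); 28 per arm if 70% are retained (0.70 × 40 = 28, from the retention criterion under Endpoints); share p of controls changing stage by a visit, assumed from 2% to 20%.

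Formulas: expected changers = n × p; probability of none = (1 − p)^n; two-sided Fisher exact test at 5%.

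Threshold against zero changers in the other arm:
- 40 per arm: 5 v 0 gives p = 0.055; 6 v 0 gives p = 0.026.
- 28 per arm: 5 v 0 gives p = 0.052; 6 v 0 gives p = 0.023.

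Six changers against none are therefore needed at either size.

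| n per arm | Assumed p | Expected changers | P(none) | P(6 or more) |
|---|---|---|---|---|
| 40 | 2% | 40 × 0.02 = 0.8 | 0.45 | <0.001 |
| 40 | 5% | 40 × 0.05 = 2.0 | 0.13 | 0.014 |
| 40 | 10% | 40 × 0.10 = 4.0 | 0.015 | 0.21 |
| 40 | 20% | 40 × 0.20 = 8.0 | <0.001 | 0.84 |
| 28 | 5% | 28 × 0.05 = 1.4 | 0.24 | 0.002 |
| 28 | 10% | 28 × 0.10 = 2.8 | 0.05 | 0.055 |

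The last column is the chance of a Fisher p value below 0.05 if singing prevented every stage change, which is the most favourable case. For a halving of the rate at 40 per arm, the normal approximation gives power of 0.06, 0.09, 0.13 and 0.24 at 2%, 5%, 10% and 20%. The exact Fisher calculation is lower: <0.001, 0.005, 0.04 and 0.16.

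Rates may be higher by 6 months than by 3. However, the waiting-list arm is to start singing after 3 months, so the 6-month comparison is no longer singing against usual care.

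**The case against.** The strongest reply is that the point matters little. This is a feasibility study with a mainly descriptive analysis and no power claim for any measure. The criteria for proceeding concern recruitment, retention and uptake after the waiting list, and none uses CDR. The Endpoints section names the "measurement of quality of life, activities of daily living, mood, musical engagement and cognition of people with dementia" and does not mention dementia severity. ADAS-Cog (to 70) and BADLS (to 60) already give finer scales, and finding that a measure is insensitive is a legitimate result of screening. All of this stands and limits the consequence.

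It could also be said that the choice of CDR summary belongs in the analysis plan. That does not stand. The article describes scoring instrument by instrument, including why COPE is analysed by subscale, and for CDR it states the overall stage.

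A reader might infer several stronger things that the documents do not support:
- **That CDR cannot register change.** No rate of change is given, and under the assumed rates some participants do change stage.
- **That eligibility leaves only two levels.** The entry criterion is not defined by CDR, and it restricts entry, so stages 0.5 and 3 can occur at follow-up.
- **That the domain ratings are thrown away.** Nothing says they are not recorded or kept.
- **That CDR misses the trial's target effect.** The 0.3 in Study objectives is for quality of life in a future trial of 360 dyads.
- **That CDR is specifically committed to ANCOVA.** The ANCOVA sentence names no instrument, and the descriptive rule for categorical variables would fit a five-level stage.

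Nor do the documents show that the domain sum is more responsive. It is finer by construction, and how it behaves is what this study could find out.

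**Conclusion.** The point holds as a minor weakness in a secondary outcome. CDR is listed as an outcome at three visits and scored only as an overall stage, which is likely to show little change or between-arm difference over 3 to 6 months. With assumed rates of 5% to 10%, only 2 to 4 of 40 controls would change, below the 6 against 0 needed for Fisher p < 0.05. This rests on those rates and on most participants starting at stage 1 or 2, which the entry criterion makes likely but does not guarantee. At an assumed 20%, complete prevention would usually be detected, although a halving still would not. The practical effect is confined to judging CDR as a candidate measure for the full trial. Recruitment, retention and acceptability are unaffected.

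**What to change.** Keep the overall CDR stage for stratification and for describing the sample. For the follow-up outcome, state that the sum of the six domain ratings will be analysed at 3 and 6 months with the baseline sum as covariate. Name all six domains and give the rating scale of each, because the section announces six and lists five.

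If the team does not want that outcome, state instead that follow-up CDR is descriptive only and not a candidate outcome for the full trial.

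The first option costs a sentence or two in the plan and six fields kept in the database, with no extra data collection because the ratings are already made. The second costs one sentence. Neither shortens the visit.
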